### Statistical Analysis

Intent-to-treat analyses will be used to include all participants with baseline and at least one follow-up value. Additional analyses will be conducted per protocol based on intervention adherence. Final selection of covariates included in the models will be based on model fit statistics, such as AIC.

#### Aim 1

Initial results for feasibility, broken down separately for number of lessons and videos accessed, activity breaks accessed, and frequency of interaction, will be expressed using contingency tables. Rates, based on a generalized linear model with a Poisson distribution, will be used to both adjust for covariates and compare the 2 versions of the app (FMS vs UPA). Each of the 4 domains of acceptability will be treated independently and considered as a continuous response, analyzed with a linear model for covariate and app effects.

#### Aim 2

FMS results will be estimated using a linear mixed effect model with the baseline and follow-up scores at week 12 (end of intervention) and week 24 (end of study) as the outcome. This model will use random effects to account for the correlation in a participant over time. Results from the model will be reported as least square means, with *P* values based on *t* tests.

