#### Reminders and Reinforcement Schedule

One-way SMS or text messages were sent 5 times each week via the mobile app to prompt the parent to read each week’s lesson (1 time/week) and to prompt the parent and child to engage in the activity break (5 times/week). Parents selected times at their screening visit of when they wanted to receive these reminders. Additionally, a reinforcement schedule was built into the PLAY study mobile app by a point system in which the child pressed a star on the screen for each day that they performed the activity break (5 stars available for each week). Parents were encouraged to reward their child with non-food–based rewards such as small toys or non-tangible items such as a high-five. A new lesson was available every 7 days for 12 weeks for 12 lessons total. Lessons were unlocked regardless of the number of activity breaks completed; parents had access to previous lessons but were unable to access future lessons until the respective week. Research assistants also monitored parents’ usage of the app weekly by monitoring whether the parents reported that the child engaged in at least one activity break through the star reporting system. The research assistants telephoned the parent when this information was missing to inquire if there were technical difficulties accessing the app.

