#### Fundamental Motor Skill (FMS) Condition

The PLAY app provided parents in the FMS condition with brief instructional lessons, peer modeling videos of FMS, and peer modeling videos of activity breaks to deliver targeted, structured FMS instruction time. The FMS condition was built on a curriculum focused on 6 key FMS (3 locomotor, 3 object control) that were selected to be challenging but developmentally appropriate (hop, throw, slide, kick, jump, catch; each repeated twice). Activity breaks were developed and tested previously in a preschool-age population, demonstrating effectiveness to improve children’s motor skill competence with good adherence [40,41]. Each week’s lesson included 6 videos; 5 videos (approximately 5 seconds in length) showed preschool-aged children performing different aspects of an FMS (eg, stepping with opposition, bending knees). These series of videos were intended to help the parent select components of the FMS to focus on to shape the child’s skill towards mastery [42]. A final video each week (<1 minute in length) showed children demonstrating activities for the activity break, which included activities that reinforced the week’s selected skill. This final video was narrated by children.

For example, on Week 1 Day 1, the parent received a notification to open the app and access the first themed lesson, “Hop.” The parent was asked to read a brief instructional lesson about the targeted FMS (including a description of a proficient “hop”), view the brief videos of the demonstrated FMS and suggested activity break activities, and then engage in a 12-minute activity break designed to help the parent model the skill and provide the preschool child with practice for the targeted FMS. Given the complexity of each FMS, parents were given 5 videos of the subcomponents of completing each FMS and asked to practice the progression that fit the child. For example, for overhand throwing, the child would practice winding up, stepping forward with the opposite foot, following through across their body, and aiming either for distance or accuracy. Therefore, the child and parent had video examples of child peers completing these FMS subcomponents. The goal was to obtain a total exposure of 720 minutes of directed instruction over 12 weeks, a dosage that aligns with prior interventions that effectively improved children’s FMS [35,43].

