#### Unstructured Physical Activity (UPA) Condition

Parents in the UPA (defined as child-led free play) condition had access to the UPA lessons and UPA activity breaks to promote the equivalent amount of UPA time for the child (ie, 720 minutes over 12 weeks). The lessons were adapted to be developmentally appropriate for preschool children using a curriculum previously developed and tested based on social cognitive theory [30]. This comparator arm was selected as it has shown to increase children’s PA levels [30] but does not explicitly target FMS or provide structured lessons to parents on how to model these skills. The following 6 topics were covered: setting goals, making time for child’s free play, being active indoors and outdoors (eg, dancing), reinforcing PA, reducing sedentary behaviors (eg, screen-time), and parental co-participation. The activity breaks provided specific strategies to encourage the child’s UPA (eg, take your child to the park or outside, use your phone alarm to remind your child to be physically active) with an accompanying video narrated by an adult that read aloud the lesson and featured photos depicting images that aligned with the lesson (eg, a photo of a park). There were no children featured in the photos so that the UPA group did not receive any peer modeling. Features of each condition may be found in Table 1.

**Table 1 table1:** PLAY app: features of each condition.

Features	Fundamental motor skills (FMS)	Unstructured physical activity (PA)
Child physical activity	720 minutes of directed instruction on FMS over 12 weeks (12 minutes/day, 5 days/week)	720 minutes of unstructured PA over 12 weeks (12 minutes/day, 5 days/week)
Parent lesson	Parent reads lesson once a week on each targeted FMS (eg, description of a proficient “hop”)	Parent reads lesson on PA support once a week (eg, how to make time for PA)
Peer modeling videos	Parent and child watch video of peers modeling each targeted FMS (eg, a child performing a “hop”)	None
Activity break	Practice, modeling, and reinforcement of each targeted FMS (eg, hopping game)	Activity breaks of unstructured PA (eg, take child to the park, play songs for a dance party)
Push notifications	Once per week to notify of lesson availability; 5 times per week to prompt each 12-minute activity break	Once per week to notify of lesson availability; 5 times per week to prompt each 12-minute activity break

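### Aim 1 compares the apps on videos accessed although FMS offers 6 a week and UPA apparently one; unless scaled to videos offered, that comparison reflects app content, not adherence

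*Protocol article*

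**What the plan says.** The Primary Outcomes section of the protocol article defines feasibility as adherence to the app. It is measured by logged counts of lessons, videos and activity breaks opened, plus the families' own star reports. Under Statistical Analysis, Aim 1, these results are first to be shown in contingency tables, "broken down separately for number of lessons and videos accessed, activity breaks accessed, and frequency of interaction". Poisson rates then follow, which "will be used to both adjust for covariates and compare the 2 versions of the app". That sentence does not repeat the list of measures, but the natural reading is that it applies to all of them. It mentions covariates, but no offset and no denominator.

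The content of the two apps is described elsewhere:

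- **FMS Condition:** "Each week’s lesson included 6 videos; 5 videos (approximately 5 seconds in length) showed preschool-aged children performing different aspects of an FMS". The sixth is described next: "A final video each week (<1 minute in length) showed children demonstrating activities for the activity break".
- **UPA Condition:** activity-break strategies come "with an accompanying video narrated by an adult that read aloud the lesson and featured photos depicting images that aligned with the lesson". No number per week is given. Table 1 shows no peer modelling videos in this arm.
- **Reminders and Reinforcement Schedule, both arms:** "A new lesson was available every 7 days for 12 weeks for 12 lessons total", with five stars to be earned each week.

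**The concern.** A count of items opened measures adherence across two groups only if both groups had the same number to open. That is true of lessons and stars. It is not true of videos, because the FMS app splits each skill into several very short clips while the UPA app appears to have a single narrated video per lesson.

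A Poisson comparison of the raw video counts would therefore favour FMS even if families in the two arms engaged equally. The usual denominators, per family or per week, are the same in both arms and do not remove this. The Discussion makes it matter more: it presents video viewing as objective evidence of app use, while completion of activity breaks rests on parent report. Video counts are thus part of the limited objective evidence on a primary outcome.

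**Working it through.** **Inputs**

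- FMS videos per week: 5 skill clips + 1 activity-break video = 6, which reproduces the article's own figure (FMS Condition).
- UPA videos per week: 1. This is an inference from a single video accompanying weekly material (UPA Condition).
- Lessons: 12 in each arm (Reminders and Reinforcement Schedule).
- Stars: 5 × 12 = 60 in each arm (same section).

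**Videos offered over 12 weeks**

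- FMS: 6 × 12 = 72.
- UPA: 1 × 12 = 12.

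**Expected rate ratio when both arms open the same share *a* of what they are offered**

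Ratio = 72*a* / 12*a* = 6.0, whatever the value of *a*:

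| Share opened, both arms | FMS videos | UPA videos | Ratio |
|---|---|---|---|
| 50% | 36 | 6 | 6.0 |
| 70% | 50.4 | 8.4 | 6.0 |
| 90% | 64.8 | 10.8 | 6.0 |

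Dividing both counts by 12 weeks leaves 6.0 unchanged. Dividing by videos offered gives (72*a*/72) / (12*a*/12) = 1.0.

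**If lessons and videos are pooled into one count**

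(72 + 12) / (12 + 12) = 84/24 = 3.5.

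**Sensitivity to the inferred UPA number**

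- Two videos a week: 72/24 = 3.0.
- One per topic, six in total: 72/6 = 12.

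**Measures with equal maxima**

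- Lessons: 12/12 = 1.0.
- Stars: 60/60 = 1.0.
- Activity breaks: both arms are asked for five days a week, and no difference in what the apps offer is stated.

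**Illustration with the planned type of model**

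Poisson models were fitted to 500 simulated trials at 28 and again at 36 dyads per arm, with each family opening a binomial number of its videos at an assumed 70% in both arms.

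| Dyads per arm | Mean ratio, no offset | Significant | Mean ratio, offset log(videos available) | Significant |
|---|---|---|---|---|
| 28 | 6.0 | 100% | 1.00 | 0% |
| 36 | 6.0 | 100% | 1.00 | 0% |

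The 0% is below the nominal 5% because binomial counts at 70% have a variance of only 1 − 0.7 = 0.3 times their mean, so the Poisson test is conservative here. The informative result is the ratio.

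**The case against.** The best reply is that the article says rates, that a rate has a denominator, and that a condensed article may leave the offset to a full analysis plan that is not shown. This stands as a limit on certainty: an offset for videos available may exist, and the distortion would then vanish. It does not dispose of the point. The article itself fixes the measure (number accessed), the model, the contrast and the unequal content, and followed as written these give a misleading video ratio under any per-family or per-week rate.

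Three stronger readings are tempting and are not supported:

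- **That a six-fold difference is certain.** The UPA count is inferred, the denominator is unstated, and Aim 1 names lessons and videos together, so a pooled count with a factor of 3.5 is possible. The Primary Outcomes section lists them separately, so the text leaves this open.
- **That the whole feasibility comparison is invalid.** Only the video component is affected. Lessons and stars have equal maxima.
- **That poor FMS adherence would be hidden.** Within the video measure it could be: if only distinct videos count, an FMS family opening 20% of its videos (0.20 × 72 = 14.4) would outscore a UPA family opening all 12. But activity breaks and interaction frequency are reported separately, and lower adherence could show there.

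Two further objections stand and shape the remedy. The FMS clips are there for parents to choose the components that suit the child, so opening all 72 is not necessarily full adherence. Earlier lessons also stay accessible; if repeat views count, the totals are not capped at 72 and 12, and a share or logit model would not fit.

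It is also fair to say that Aim 1 states no hypothesis of a difference between apps and that the article ties no decision threshold to this test. That limits the consequence but does not make the ratio interpretable.

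**Conclusion.** The point holds in conditional form. If the video rate is not scaled to what each arm offered, equal proportional use would give a rate ratio of about 6, or 3.5 if lessons and videos are pooled. The figure of 6 assumes one UPA video per weekly lesson; with two a week it is 3.0, and with one per topic it is 12. Under each of these readings the ratio is well above 1 in favour of FMS and comes from app content, not adherence.

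The fault is confined to the video component of feasibility. It should be corrected because feasibility is a primary outcome, the article reports that its analysis was still under way, and the remedy is nearly free.

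**What to change.** In the Aim 1 analysis text:

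1. Analyse videos separately from lessons.
2. Base the between-app comparison of adherence on lessons, activity breaks and stars.
3. For videos, either report use descriptively within each arm or keep the Poisson model with log(number of videos available in that arm) as an offset, and state that number for UPA.
4. State whether accessed means distinct videos opened or all views. Use a share of videos opened, or a logit model for it, only in the first case.

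The cost is a change of wording and a rerun on usage logs that the app developer already supplies. The small downside is that the between-app video comparison is dropped or rescaled. Even rescaled, it should be read with care, because FMS parents were meant to choose among clips and full viewing is not a clear standard of adherence.

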**Methods:**

We conducted a 2-arm, parallel-design, randomized comparative effectiveness trial in 72 parent-child dyads from the southeastern United States. Experts in motor development and developmental psychology developed an app designed to deliver a 12-week program to parents of preschoolers using 1 of 2 curricula: an FMS program (intervention) that involved peer modeling, parent engagement, and structured skills-based activities and an unstructured physical activity (comparator) curriculum that provided suggestions for child-led physical activity (ie, free play). Primary outcomes are feasibility and acceptability of the app and child’s FMS measured at end of intervention (week 12). Exploratory outcomes are child’s objective physical activity, perceived movement competence, and parent report of self-regulation at the end of treatment (week 12) and sustained outcomes at follow-up (week 24).

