### Measures

#### Primary Outcomes

Feasibility was measured as adherence to the mobile app intervention, including objective data on the number of lessons, videos, and activity breaks accessed, and self-reported frequency of interaction with the app through the reinforcement schedule (ie, star reporting system). These data were provided on an ongoing basis by CyberFision. Acceptability was captured at weeks 4, 8, and 12 with an in-app parent survey that assessed satisfaction with the intervention in 4 domains (overall satisfaction, helpfulness, ease of use, and perceived change in child’s motor skills) using a Likert-type scale. The System Usability Scale [48] and a satisfaction scale [49] were completed by the parents at the week 12 and 24 assessment visits. Additional usage data were captured via weekly parent surveys embedded within the app: the context of the activity breaks including the parent’s location, the child’s location, and who participated (weeks 1, 5, 9); barriers to performing the activity breaks and the use of equipment during the breaks (weeks 2, 6, 10); and engagement with the mobile app (weeks 3, 7, 11).

FMS were assessed using the TGMD-3, a direct observation assessment used with children aged 3-10 years [37]. The TGMD-3 is a process-oriented and product-oriented assessment to evaluate FMS performance in 2 subscales: locomotor (run, gallop, one-legged hop, skip, jump, and slide) and ball skills (two-hand strike, one-hand strike, catch, kick, dribble, overhand throw, and underhand throw). By design, these include skills targeted in the intervention. Previous research has demonstrated that the TGMD-3 is a valid and reliable assessment tool [50,51]. Assessments were filmed in an open space and coded by trained research assistants blinded to the purpose of this project. An FMS expert ([name]), who previously attained 99% reliability coding with the author of the TGMD-3 assessment, coded the administrations and was blinded to the experimental condition of the participants.

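### Feasibility counts are compared with a Poisson model although stars and distinct lessons are bounded, so the standard errors may be too small or too large unless dispersion is handled

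*Protocol article*

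**What the plan says.** The abstract lists feasibility and acceptability among the primary outcomes. Under Measures, Primary Outcomes, feasibility is adherence, made up of "objective data on the number of lessons, videos, and activity breaks accessed, and self-reported frequency of interaction with the app" through the star system.

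Under Statistical Analysis, Aim 1, these measures are first shown in contingency tables. For the comparison of the two arms the article then states: "Rates, based on a generalized linear model with a Poisson distribution, will be used to both adjust for covariates and compare the 2 versions". It names no dispersion parameter, robust variance or random effect for Aim 1. For Aim 2, in the next paragraph, it does name random effects.

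Two of the counts have a known maximum under Reminders and Reinforcement Schedule:

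- Lessons: "A new lesson was available every 7 days for 12 weeks for 12 lessons total".
- Stars: "5 stars available for each week", which over 12 weeks gives 5 × 12 = 60.

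The same section says that "parents had access to previous lessons but were unable to access future lessons until the respective week", so raw access counts need not stop at these figures.

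On acceptability, "Acceptability was captured at weeks 4, 8, and 12 with an in-app parent survey". Each of the four domains is to be "considered as a continuous response, analyzed with a linear model for covariate and app effects".

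**The concern.** A Poisson variance equals the mean. Two features of these counts pull away from that. A total with a ceiling varies less than a Poisson count as completion approaches the ceiling. Differences between families in how much they use the app push the variance up. The two effects cancel only by coincidence, and the point at which they cancel differs between a count out of 12 and a count out of 60.

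At stake is the between-arm comparison on a primary outcome. If the standard error is too small, one version of the app could be declared more used when the two do not differ. If it is too large, a real difference in lesson access could be missed.

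Acceptability raises a smaller, conditional question. The same parent answers at three waves, and a linear model with no parent term would treat the answers as independent if the waves were analysed together.

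**Working it through.** The article gives no rate, variance or power figure for the feasibility comparison, so there is no stated number to reproduce.

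**Inputs from the article.** Maximum m = 12 for distinct lessons and m = 60 for stars; 36 dyads per arm (Study Design).

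**Assumed inputs.** Mean completion p = 0.6 to 0.7 and intra-family correlation ρ = 0.1 to 0.2. The same ρ is used for lessons and stars because they come from the same families.

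**Variance ratio.** For one total per dyad out of m opportunities (beta-binomial), the mean is mp and the variance is mp(1−p)[1+(m−1)ρ]. The Poisson variance is mp. Hence

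ratio = (1−p)[1+(m−1)ρ].

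A nominal 5% Wald test that uses the Poisson variance has true type I error 2[1−Φ(1.96/√ratio)].

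| Count | p | ρ | Ratio | Type I error |
|---|---|---|---|---|
| Stars, m = 60 | 0.7 | 0.1 | 0.3 × 6.9 = 2.07 | 17.3% |
| Stars | 0.7 | 0.2 | 0.3 × 12.8 = 3.84 | 31.7% |
| Stars | 0.6 | 0.1 | 0.4 × 6.9 = 2.76 | 23.8% |
| Stars | 0.6 | 0.2 | 0.4 × 12.8 = 5.12 | 38.6% |
| Lessons, m = 12 | 0.7 | 0.1 | 0.3 × 2.1 = 0.63 | 1.4% |
| Lessons | 0.7 | 0.2 | 0.3 × 3.2 = 0.96 | 4.6% |
| Lessons | 0.6 | 0.1 | 0.4 × 2.1 = 0.84 | 3.3% |
| Lessons | 0.6 | 0.2 | 0.4 × 3.2 = 1.28 | 8.3% |

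**Break-even.** Setting the ratio to 1 gives ρ = p/[(1−p)(m−1)]. At p = 0.7 this is 0.7/(0.3 × 11) = 0.21 for lessons and 0.7/(0.3 × 59) = 0.04 for stars. At 70% completion, any ρ between 0.04 and 0.21 makes the lesson standard error too wide and the star standard error too narrow in the same trial. Any single count errs in one direction only.

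**Simulation check.** With 36 dyads per arm and 3,000 null trials per scenario, p = 0.7 and ρ = 0.1:

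| Count | Plain Poisson | Quasi-Poisson | Robust |
|---|---|---|---|
| Stars | 16.9% | 5.3% | 5.5% |
| Lessons | 1.2% | 4.4% | 4.7% |

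Across nine scenarios (p from 0.5 to 0.9, ρ from 0 to 0.5) plain Poisson ran from 0.0% to 50.6%. The two corrected methods stayed between 4.0% and 5.8%.

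**Acceptability, only if the three waves are pooled.** With an assumed within-parent correlation of 0.5, the variance inflation for an arm effect is 1 + 2 × 0.5 = 2.0. Type I error is then 2[1−Φ(1.96/√2)] = 16.6%.

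**The case against.** The best defence is that naming a Poisson family does not exclude a scale parameter or a robust variance, and that a condensed article may leave such detail to the full protocol or analysis plan. Robust standard errors would fit the quoted sentence unchanged. This stands in part: the article does not say that the variance will be left uncorrected. But it does choose a distribution that ties variance to mean for bounded counts, and says nothing to relax it. The point therefore concerns a stated choice and not only an absent detail.

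Aim 1 is also worded as an examination of feasibility, with no between-arm hypothesis, and the contingency tables do not use the Poisson variance. That limits the consequence to the arm comparison.

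A reader might infer more than the article supports, in four respects:

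- **That the errors are known to be wrong in both directions.** Size and direction depend on adherence and heterogeneity, which are not given. At p = 0.7 and ρ = 0.2 the Poisson standard error for lessons is about right. A lesson type I error near 0.1% needs a much lower correlation (0.02 at p = 0.7) than the one assumed for stars.
- **That some families do nearly everything and others nearly nothing.** Variation between families is likely, but the article does not describe it.
- **That logged activity breaks are capped at 60.** Only stars and distinct lessons have a certain maximum, because earlier lessons can be reopened.
- **That the acceptability waves are pooled.** The article says only that the domains are handled separately. Separate models per wave, or week 12 alone, would also fit.

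**Conclusion.** The point holds in a limited form. Taken as written, the Poisson comparison has correct standard errors only at a break-even level of between-family variation that differs between lessons and stars. Under assumed completion of 60% to 70% and ρ of 0.1 to 0.2, star standard errors are too small, with variance ratios of 2.07 to 5.12 and type I error of about 17% to 39%. For lessons at 70% completion they are too large to about right, with ratios of 0.63 to 0.96 and type I error of about 1.4% to 4.6%; at 60% completion the lesson error could fall on either side.

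All these sizes are illustrations that rest on assumed p and ρ and on a beta-binomial total per dyad. They show what could happen, not what did. The acceptability point applies only if the waves are analysed together. The change is worth making because the outcome is primary and the remedy is cheap.

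**What to change.** Keep the log-linear rate model and state that all feasibility counts (lessons, videos, activity breaks, stars) will be analysed with robust (sandwich) standard errors or a quasi-Poisson scale. Apply this to one total per dyad; if weekly records are modelled, cluster the robust errors by dyad. For stars (of 60) and distinct lessons (of 12) only, where the denominator is known, a quasi-binomial or beta-binomial model is an alternative. It should not be used for raw access counts, which may exceed those figures.

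For acceptability, include a parent random effect if weeks 4, 8 and 12 are analysed together; otherwise analyse week 12 alone.

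The cost is a sentence of analysis text and a model option, with no new data. Intervals for overdispersed counts become wider by the square root of the variance ratio: √2.07 = 1.44 to √5.12 = 2.26 times in the star scenarios above, and less where overdispersion is milder. Lesson intervals at 70% completion become narrower (√0.63 = 0.79 to √0.96 = 0.98 times). A quasi-Poisson fit has no ordinary AIC, which the article cites for choosing covariates, so that option would also need a quasi-likelihood criterion or covariates fixed in advance.

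### Acceptability is rated three times per parent, but the linear model stated for it has no survey week and no parent-level term

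*Protocol article*

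**What the plan says.** The abstract lists acceptability among the primary outcomes: "Primary outcomes are feasibility and acceptability of the app and child’s FMS measured at end of intervention (week 12").

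Under Primary Outcomes in the Measures section, the schedule is: "Acceptability was captured at weeks 4, 8, and 12 with an in-app parent survey that assessed satisfaction with the intervention in 4 domains". Each parent can therefore give up to three ratings per domain. Two further instruments are collected at visits: "The System Usability Scale [48] and a satisfaction scale [49] were completed by the parents at the week 12 and 24 assessment visits".

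Under Statistical Analysis, Aim 1, the analysis is: "Each of the 4 domains of acceptability will be treated independently and considered as a continuous response, analyzed with a linear model". The only effects listed for it are covariates and the app version. No survey week is chosen and no summary across weeks is defined.

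Under Aim 2, the motor-skill score gets a linear mixed model over its visits, with the reason given: "This model will use random effects to account for the correlation in a participant over time". The exploratory outcomes are to be analysed in a similar way.

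The opening of Statistical Analysis defines the intent-to-treat set as participants with a baseline value and one or more follow-up values.

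**The concern.** Three ratings from one parent are correlated. An ordinary linear model with no parent-level term is valid only if each parent contributes one value. The article recognises this for motor skills, activity, perceived competence and self-regulation, but states a model without such a term for acceptability, a primary outcome that is also repeated. An analyst following the text has three choices:

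- stack all three ratings, which misstates precision;
- take week 12, which drops parents who answered earlier and then stopped;
- average within parent, which compares averages taken over different weeks for different parents.

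These can give different answers, and the article does not say which is meant.

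There is a second difficulty. The survey is delivered in the app, so a parent has to open the app to answer it, and a mean over responders need not describe all randomized parents. The stated intent-to-treat set does not help, because satisfaction with the intervention, first asked at week 4, has no baseline value.

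**Working it through.** The article gives no sample size, power or error rate for acceptability, so there is no stated figure to reproduce. The check is what each reading of the text would do.

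**Inputs**
- Ratings per parent and domain: m = 3 (weeks 4, 8, 12; Primary Outcomes).
- Parents: 72 randomized 1:1, so 36 per arm; 28 per arm planned as evaluable at week 12 (Sample Size and Power Calculation).
- Within-parent correlation ρ: not given. Assumed exchangeable, 0.5 to 0.7, with 0.3 to 0.8 as a wider range.
- In-app survey response rate: not given.

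**Reading 1: all three ratings stacked as independent**

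With full response, 72 × 3 = 216 ratings come from 72 parents. The variance of the difference between arms is understated by the design effect DE = 1 + (m − 1)ρ = 1 + 2ρ. The standard error is too small by 1 − 1/√DE, and the actual two-sided error rate of a nominal 5% test is 2 × [1 − Φ(1.96/√DE)].

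| ρ (assumed) | DE | SE too small by | 1.96/√DE | Actual error rate |
|---|---|---|---|---|
| 0.3 | 1.6 | 21% | 1.550 | 0.121 |
| 0.5 | 2.0 | 29% | 1.386 | 0.166 |
| 0.7 | 2.4 | 35% | 1.265 | 0.206 |
| 0.8 | 2.6 | 38% | 1.216 | 0.224 |

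A simulation with no true difference (20,000 runs per setting) agrees. For ρ of 0.3, 0.5 and 0.7, the stacked t test rejects in 0.123, 0.171 and 0.209 of runs with 28 parents per arm, and in 0.121, 0.170 and 0.211 with 36 per arm.

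**Reading 2: week 12 only**

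One value per parent. In the same simulation the rejection rate is 0.048 to 0.051, so the linear model is valid on this point. A parent who answered at weeks 4 and 8 but not at week 12 contributes nothing.

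**Reading 3: mean of the available ratings per parent**

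With three ratings for every parent, the rejection rate is 0.048 to 0.053. With missing surveys, a parent with only a week-4 rating is compared with parents averaged over all three weeks.

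**Analysis set**

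The intent-to-treat rule needs a baseline value plus a follow-up value. The first acceptability survey is at week 4, so the rule cannot be applied to this outcome as written.

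**The case against.** A reader might infer from the contrast with Aim 2 that the plan will stack the ratings and ignore their correlation. The document does not say so. The words about independent treatment refer to the four domains, not to the three survey times. The abstract's sentence on primary outcomes can be read as placing acceptability at week 12, which would give one value per parent and a valid linear model, although the time phrase may belong to the motor-skill score alone. The error rates of 17% to 21% therefore rest on two things the article does not state: stacking, and the assumed correlation. This objection stands, and the finding is worded conditionally because of it.

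A reader might also infer that later ratings come from more satisfied parents. In-app delivery makes selective response plausible, but no response rate and no link to satisfaction is given. Staff telephoned parents who reported no activity in a week, and the Results section reports completed data collection on 69 dyads. Neither fact establishes in-app survey response, and neither suggests heavy loss. The direction and size of any bias stay unknown.

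Using one week rather than three is an efficiency choice, not an error in itself. This is a pilot, and the article ties no success threshold to this comparison.

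Finally, an article may leave the choice of week or summary to the full plan. That weakens any complaint about missing detail. It does not remove the point, because the article does name a model and its effects, and a better-suited one stands in the next paragraph.

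**Conclusion.** The point holds in conditional form and the change should be made. The stated model is not tied to the three survey times. Under stacking, with ρ of 0.5 to 0.7, precision is overstated (standard errors 29% to 35% too small) and the error rate is about 17% to 21%; over ρ of 0.3 to 0.8 it is about 12% to 22%. Under a week-12 analysis the error rate is correct, but early ratings from parents who stop answering are lost and the estimate is restricted to week-12 responders. The document does not establish which reading is intended, so it cannot be said that the planned test is invalid. That the intent-to-treat set does not fit an outcome without a baseline holds under every reading.

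**What to change.** For each domain, replace the linear model with the approach already used for Aim 2: a mixed model with app, survey week, app-by-week, the planned covariates and a parent random effect, reporting the week-12 contrast between apps. This is valid for repeated ratings and keeps the week-4 and week-8 ratings of parents who stop answering.

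Define the acceptability analysis set as every parent with at least one rating, analysed as randomized. Report survey response rates by arm and week. Present the System Usability Scale and satisfaction scale from the week-12 visit alongside, since they do not depend on opening the app, although they do depend on attending the visit.

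State the limit of the model: it reduces responder selection only if missingness depends on ratings already observed. It does not remove bias if parents stop because of dissatisfaction not yet recorded, and it adds nothing for parents who never respond.

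The cost is a few sentences of analysis-plan wording. The surveys and visit scales are already part of the data collection, which the article reports as finished with analysis under way, so no new data are needed.
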